#### CHWs and supervisors

Service delivery and implementation outcomes are ascertained from CHWs and CHW supervisors. CHWs and supervisors age ≥ 18 who are working in communities linked to the study facilities are eligible to participate in the study.

### Who will take informed consent? {26a}

#### In-depth pregnant cohort, CHWs, and supervisors

Following initial recruitment, a verbal explanation of the study is provided by study staff and verbal consent is sought to conduct eligibility screening. If the participant is eligible, written consent is obtained electronically by study staff at the time of recruitment, using REDCap [45]. Participants are informed that participation is completely voluntary and that they are free to decline participation without losing their regular medical care or their employment. Pregnant women age < 18 are considered emancipated minors under Kenyan regulations so a waiver of parental permission was obtained for these participants to allow them to provide consent independently.

#### Mortality cohort

Neonatal mortality is ascertained using abstracted, deidentified data from the eCHIS database for clients of CHWs affiliated with study facilities. These participants are not enrolled in the study as human subjects and do not provide consent for study activities.

#### Additional consent provisions for collection and use of participant data and biological specimens {26b}

N/a. The study is not collecting biological specimens.

## Interventions

### Explanation for the choice of comparators {6b}

Randomization is at the level of the healthcare facility. A cluster-randomized design is used in which entire facilities are randomized because the intervention impacts CHW workflow and therefore affects all households under their care rather than individual clients. The comparison control treatment is the standard of care version of eCHIS which is currently being used by CHWs across Kenya. eCHIS guides CHWs through completing home visits, with a range of workflows including maternal health, child health, nutrition, malaria, and water sanitation and hygiene [46]. This version of eCHIS has no SMS communication between CHWs and clients. In both study arms, antenatal and maternal and child health clinical services continue to be provided through MOH clinics with minimal interactions with study personnel.

### Intervention description {11a}

Intervention sites utilize a modified version of eCHIS which has SMS messaging incorporated as an additional module (CHV-NEO).

#### SMS curriculum

The CHV-NEO SMS intervention is based on the content of the Mobile WACh NEO intervention [41], with adaptations for this study guided by input from perinatal clients, nurses, CHWs, and CHW supervisors in formative interviews and focus groups. The intervention is based on the Information, Motivation, Behavioral skills model of behavioral change [47], with the goal of improving the provision of preventative ENC, identification of illness, and care-seeking if needed (Fig. 2). Clients receive a curriculum of pre-composed SMS messages automatically sent on a schedule starting at 28 weeks gestation and extending until 6 weeks postpartum. Clients can send an SMS at any time and their message will be read and manually responded to by the CHW who routinely conducts their home visits. Automated messages are sent in English, Luo, or Kiswahili depending on the participant’s preference. Sending and receiving SMS is at no cost to the participant or the CHW.

**Fig. 2 Fig2:**
[figure not shown]
Intervention conceptual framework

Automated SMS topics and schedule are summarized in Fig. 3, based on the client’s gestational age, date of delivery, and delivery outcome, obtained from eCHIS. From enrolment until 38 weeks gestation, automated SMS are sent weekly, encouraging facility delivery and birth planning, and providing anticipatory guidance about neonatal danger signs and emotional support. From 38 weeks gestation until delivery, automated SMS are sent daily, with similar content and highlighting neonatal danger signs and ENC practices, including immediate and exclusive breastfeeding, thermal, and cord care. From delivery to 2 weeks postpartum, two messages are sent per day: one message with screening questions regarding neonatal danger signs and encouragement to message if they have a concern and one message with educational content on postpartum care and complications, ENC practices, and emotional support. From 2 to 6 weeks postpartum, SMS are delivered every other day. Additionally, based on input from perinatal clients, CHWs, and policymakers in formative design activities, clients receive a reminder message when they are referred to the healthcare facility by the CHW, when they are due for their 6-week postpartum facility visit, and when a CHW is scheduled to conduct a home visit. All messages open with the participant’s name, state that the message is from their CHW, and contain a question to engage women in conversation. Clients who deliver a preterm or low birthweight baby receive a modified track of messages, which includes information about additional care for small and preterm babies, including Kangaroo Mother Care. Clients who experience a stillbirth or neonatal death receive a 4-week curriculum of weekly bereavement messages which provide condolences and emotional support; messages related to the infant are stopped. The message bank is available upon request.

**Fig. 3 Fig3:**
[figure not shown]
SMS curriculum overview

Message content and schedule were developed by a group of content experts on the study team. Messages are based on the Mobile WACh NEO intervention [41], with the following modifications to account for the shift from nurse to CHW delivery and to respond to stakeholder input in our formative design activities. Terminology in the messages was simplified to remove technical clinical terms and better align with lay vocabulary used by CHWs. To align with CHWs’ preventative service focus, additional messages were added antenatally providing anticipatory guidance for ENC, nutrition counseling, and reminders about family planning. To align with CHWs’ referral responsibilities and limited diagnostic role, message language requesting participants describe symptoms of illness was removed and replaced with a recommendation to seek facility-based care in case of health concerns. Discussion of mental health topics was removed due to CHW input that they did not feel comfortable responding to in-depth messages about mental illness; instead, emotionally supportive language such as “I am here for you” was increased. Additionally, based on findings from the Mobile WACh NEO trial, the frequency of antenatal messages with anticipatory guidance related to trial outcomes, particularly infant danger signs, was increased, while the frequency of messages encouraging facility delivery was decreased, given the high rates of facility delivery currently in Kenya (> 80%) [43].

#### Integration of SMS into *eCHIS* application

In partnership with the Kenyan Ministry of Health, SMS messaging functionality was integrated into the eCHIS software platform as a module of the existing interface (Fig. 4). Consenting and enrollment to communicate by SMS with the CHW was added as a required step in the standard antenatal home visit workflow among intervention CHWs, and an additional functionality was added to update client phone number, SMS language, or messaging preferences after enrollment as needed. Templates for CHW replies to frequently asked client questions were incorporated as a “FAQ” module with a topically organized bank of editable message templates in English, Swahili, and Luo (Fig. 4).

**Fig. 4 Fig4:**
[figure not shown]
Screenshots of SMS components of eCHIS

In addition to integrating SMS functionality into CHW workflows, we incorporated supervision of SMS messaging into the workflows of CHW supervisors. As part of their monthly supervision workflow, supervisors are prompted to review a CHW’s messaging, ask them if they have experienced any challenges with messaging, and support them in problem-solving any challenges.

#### Training and launch activities

The study provided training to CHWs and supervisors at the study launch on the following topics. All CHWs and supervisors in control and intervention clusters received a 2.5-day training on how to use eCHIS. Those in intervention clusters received an additional day of training on how to use the CHV-NEO SMS workflows in eCHIS. To ensure a baseline level of clinical knowledge related to maternal and neonatal health, all CHWs in both arms also received a half-day refresher training on their clinical responsibilities related to antenatal and postnatal care, newborn health, and maternal mental health.

As part of training, CHWs were instructed to sync their eCHIS application with the server daily, respond to clients by SMS within 24 h, refer to the facility if any unusual symptoms are reported by SMS or if they were unsure how to respond, seek advice from their supervisors if they have challenges with any workflows, and report any technical issues to the study team.

### Criteria for discontinuing or modifying allocated interventions {11b}

#### SMS withdrawal

Clients in the intervention group may withdraw from receiving SMS messages at any time by either sending a SMS with the word “stop” or asking their CHW to stop their messaging. Participants who withdraw from SMS can continue or withdraw from study activities.

#### Study withdrawal

Participants may withdraw from the study at any time for any reason. Study staff record the timing and reason for any early terminations. All data collection will be discontinued at the time of withdrawal. Participants who withdraw from study activities can continue or withdraw from the SMS program.

### Strategies to improve adherence to interventions {11c}

CHWs in Kisumu County receive routine supervision to support their service delivery, in the form of monthly group meetings and individual meetings between CHWs and their supervisor. The study carries out the following additional quality assurance activities. At monthly group meetings, the study shares a report on aggregate CHW performance in terms of completeness of eCHIS data related to pregnancies and newborns and, at intervention facilities, SMS messaging process indicators. Additionally, the study team conducts a monthly review of a sample of CHWs’ SMS exchanges with clients. Clinical experts on the study team review CHW message timeliness and appropriateness per standards set forth in prior Mobile WACh studies [37, 41]. Summary data from these reviews and feedback for CHW responses are shared with CHWs and their supervisors at the monthly supervision meetings. The same data is also shared with Kisumu County leadership at separate regular meetings.

### Relevant concomitant care permitted or prohibited during the trial {11d}

Perinatal women participants in both arms continue to receive all standard healthcare services from local healthcare facilities. The study provides no clinical care.

### Provisions for post-trial care {30}

Participants continue with services as usual post-trial.

### Outcomes {12}

#### Clinical outcomes

Primary, secondary, and exploratory clinical outcomes are summarized in Table 1. The primary outcome is neonatal mortality, defined as the death of a live-born infant within 28 days of birth, based on routine data abstracted from eCHIS during the study period. Secondary outcomes are ascertained among the in-depth perinatal cohort who complete study questionnaires. Secondary outcomes were selected based on the intervention’s hypothesized mechanism of action (Fig. 2) and their importance as intermediate outcomes in neonatal survival. These include initiation of breastfeeding within the first hour of life (ascertained by maternal self-report at the 6-week postpartum study visit); application of substances to cord (ascertained by maternal self-report at the 6-week visit); maternal knowledge of neonatal danger signs (defined as the number of the eight neonatal danger signs correctly named at the 6-week visit); and appropriate care seeking (defined as the proportion of illness episodes with danger signs where the infant attended the clinic, based on maternal self-report at the 6-week visit). Exploratory clinical outcomes include mothers’ identification of danger signs in their infants (defined as the proportion of all infants whose mothers report they ever exhibited a danger sign at the 6-week visit); infant hospital admissions (based on maternal self-report); and neonatal care delays (defined as the proportion of neonatal deaths attributable to each delay in the three delays model, based on review of adverse event reports by nurses and physicians on the study team).

**Table 1 Tab1:** Trial outcomes

Outcome	Indicator	Source and timing	Statistical analysis
Primary clinical outcome			
Neonatal mortality	Death during the first 28 days of life	eCHIS routine data throughout 2 years of study implementation	GLMM (RE by facility and CHW) with Poisson link and survival time as offset
Secondary clinical outcomes			
Initiation of early breastfeeding	Breastfed in the first hour of life	Questionnaire at 6-week visit	GLMM (RE by facility and CHW) with Poisson link and robust SE
Appropriate cord care	Application of nothing or chlorhexidine to umbilical cord	Questionnaire at 6-week visit	GLMM (RE by facility and CHW) with Poisson link and robust SE
Appropriate thermal care	No bath in the first 24 h of life	Questionnaire at 6-week visit	GLMM (RE by facility and CHW) with Poisson link and robust SE

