**Methods:**

The effect of CHV-NEO on clinical and implementation outcomes will be evaluated through a non-blinded cluster randomized controlled trial. Twenty sites across Kisumu County in Western Kenya were randomized 1:1 to provide either the national eCHIS with integrated CHV-NEO messaging (intervention) or standard of care using eCHIS without CHV-NEO (control). We will compare neonatal mortality between arms based on abstracted eCHIS data from 7200 pregnant women. Secondary outcomes include self-reported provision of essential newborn care (appropriate cord care, thermal care, and timely initiation of breastfeeding), knowledge of neonatal danger signs, and care-seeking for neonatal illness, compared between arms based on questionnaires with a subgroup of 2000 women attending study visits at enrollment in pregnancy and 6 weeks postpartum. We will also determine CHV-NEO’s effect on CHW workflows and evaluate determinants of intervention acceptability, adoption, and fidelity of use through questionnaires, individual interviews, and messaging data.

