#### Pregnant women—mortality cohort

Outcomes are ascertained from two nested cohorts of pregnant women (Fig. 1). The primary clinical effectiveness outcome (neonatal mortality) is ascertained using abstracted routine data from the eCHIS platform in all study sites. Inclusion criteria for these women are being registered as pregnant in eCHIS at gestational age ≤ 36 weeks by a CHW linked to a study facility.

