### Sample size {14}

Our study is powered for primary and secondary clinical outcomes. The cluster-randomized trial includes 20 facility clusters, 10 interventions, and 10 controls. For ascertainment of our primary outcome of neonatal mortality, we will abstract outcomes from eCHIS on 7200 pregnancies ending in live births across the clusters. With this sample size, assuming *α* = 0.05, two-sided tests, 10% attrition, a conservative coefficient of variation of 0.25, and assuming unequal cluster sizes with an average cluster size 360, we have 80% power to detect a difference in neonatal mortality of 21.0 vs. 10.3 per 1000 live births [43]. For ascertainment of secondary outcomes, we will enroll 2000 pregnant clients in the in-depth perinatal cohort. With this sample size, assuming *α* = 0.05, two-sided tests, 10% attrition, coefficient of variation of 0.25, and unequal cluster sizes (ranging between 80 and 120 per cluster), we have 80% power to detect a difference in early initiation of breastfeeding, thermal care, and cord care of 50% vs. 72%. We expect the outcomes of appropriate care-seeking and knowledge of danger signs to be correlated so we will correct these analyses for multiple comparisons. Assuming a Bonferroni-adjusted *α* = 0.025, we will have 80% power to detect a difference between arms of 2.0 vs. 2.4 danger signs named and 0.5 vs. 0.9 appropriate clinic visits attended in the first 6 weeks [6, 37, 49, 50].

Service delivery and implementation outcomes are ascertained among the in-depth perinatal cohort as well as all CHWs and supervisors providing services over the 2-year period (estimated sample size 700 CHWs and 40 supervisors). Quantitative and qualitative analyses of implementation outcomes are intended to be exploratory; no formal hypothesis testing will be performed. We expect sample sizes for qualitative interviews will be sufficient to reach theoretical saturation of themes [51].

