#### Adverse event reporting and harms {22}

Adverse events among perinatal women, CHWs, or supervisor participants are elicited at all study visits and may also be reported spontaneously if a participant contacts the team. All adverse events are recorded by study staff using an electronic REDCap questionnaire based on a phone conversation with the participant. Events to be monitored include maternal and infant death, maternal and infant hospitalization, pregnancy loss, experience of violence, losing housing, breach of confidentiality, and suicidal behavior. Adverse event monitoring in the mortality cohort is more limited because the study will not have direct contact with these individuals. Events monitored in this cohort include maternal and infant death, pregnancy loss, and report of maternal postpartum danger signs at home visits, abstracted from eCHIS. Adverse and severe adverse events will be monitored by the study team, reported to ethical review boards as needed, and unblinded results will be reviewed by the DSMB. The DSMB will make recommendations regarding any imbalances in safety outcomes.

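### The primary outcome is confined to live births in a cohort entered during pregnancy, so a shift between stillbirth and early neonatal death could bias it, and no stated analysis would show this

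*Protocol article*

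**What the plan says.** Under Eligibility criteria, women enter the mortality cohort by "being registered as pregnant in eCHIS at gestational age ≤ 36 weeks by a CHW linked to a study facility". Under Clinical outcomes, the primary outcome is "defined as the death of a live-born infant within 28 days of birth, based on routine data abstracted from eCHIS during the study period". Table 1 models it with a Poisson mixed model, random effects for facility and CHW, and survival time as offset. A stillbirth contributes neither an event nor follow-up time to that model.

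The Intervention description starts messages at 28 weeks of gestation. The antenatal content includes birth planning and facility delivery, and the abstract adds maternal danger signs. The blinding section states that the trial is open. Recruitment and data collection make clear that the mortality data are routine eCHIS records arising from CHWs' home visits.

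Table 1 lists no stillbirth, perinatal or all-pregnancy outcome. The only additional arm comparison of mortality stated as intention-to-treat support is a multiple-imputation analysis of missing 28-day status. Pregnancy loss is abstracted for this cohort, but under Adverse event reporting: "Events monitored in this cohort include maternal and infant death, pregnancy loss, and report of maternal postpartum danger signs at home visits".

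On the denominator, the sample size section says "we will abstract outcomes from eCHIS on 7200 pregnancies ending in live births across the clusters", while the abstract says "We will compare neonatal mortality between arms based on abstracted eCHIS data from 7200 pregnant women".

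**The concern.** Whether a pregnancy contributes to the primary analysis depends on an event that follows randomisation and up to about 12 weeks of messaging (28 to 40 weeks). Two mechanisms could move the result.

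- **Real shift.** If the messages avert some stillbirths, fragile infants join the intervention arm's live births. Some die as neonates, which masks or reverses a benefit.
- **Recording shift.** A baby who dies at or just after birth may be entered as a stillbirth or as a neonatal death. If intervention CHWs choose stillbirth more often, an apparent benefit appears. The opposite habit hides one.

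Deaths among live births cannot by themselves distinguish either mechanism from prevention of neonatal deaths. The trial expects few primary events, so small shifts count.

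**Working it through.** **Inputs from the protocol.** 10 clusters per arm; average size 360; 10% attrition, so m = 360 × 0.9 = 324; coefficient of variation k = 0.25; two-sided α = 0.05; rates 21.0 and 10.3 per 1000 live births. Not in the protocol, hence assumed: the share of deaths misrecorded, the stillbirth rate, the share of stillbirths averted, and the share of those infants who die as neonates.

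**1. The plan's own figure.** The standard unmatched cluster formula is

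v = [p0(1−p0) + p1(1−p1)]/m + k²(p0² + p1²), z = √[(c−1)(p0−p1)²/v], power = Φ(z − 1.96).

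- v = 0.030753/324 + 0.0625 × 0.00054709 = 0.0000949 + 0.0000342 = 0.0001291
- z = √(9 × 0.00011449/0.0001291) = 2.83
- power = Φ(0.87) = 81%

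The stated 80% is reproduced. Expected deaths are 3240 × 0.021 = 68 and 3240 × 0.0103 = 33.

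**2. Recording shift, no true effect.** If a share d of intervention-arm neonatal deaths is entered as stillbirths, those babies leave both numerator and denominator: ratio = (1−d)/(1−0.021d). The chance of a significant benefit comes from the formula in step 1.

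| d (assumed) | Deaths moved (68 × d) | Apparent rate per 1000 | Rate ratio | Chance of false benefit |
|---|---|---|---|---|
| 5% | 3 | 20.0 | 0.95 | 4% |
| 10% | 7 | 18.9 | 0.90 | 7% |
| 20% | 14 | 16.9 | 0.80 | 16% |

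A simulation (gamma-distributed cluster rates with k = 0.25, cluster-level t test, assumed stillbirth rates of 15 and 25 per 1000) gave 4%, 7% and 16%. A separate run put the last figure at 15–16%.

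**3. Real shift.** Per 1000 pregnancies let s be stillbirths, L = 1000 − s, and a = s × share averted, with a share r of those infants dying as neonates. The intervention rate is (pL + ar)/(L + a), where p is the rate among the other live births. Ranges: s = 15–25, 10–30% averted, r = 10–50%.

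- No other effect (p = 0.021): 21.1 to 24.7 per 1000, ratio 1.01 to 1.17.
- Design effect true (p = 0.0103): the rate rises from 10.3 to between 10.4 and 14.0, and power falls from 81% to between 79% and 41%.
- Middle case (s = 20, 20% averted, r = 30%): (0.0103 × 980 + 4 × 0.3)/984 = 11.5 per 1000, power 69%.

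**4. What a composite would show.** Stillbirth plus neonatal death per registered pregnancy does not change when a death moves between the two labels. In the simulation with d = 20%, the live-birth ratio averaged 0.82 and the composite 1.01. The price is dilution. With the design effect true and stillbirth unchanged at 20 per 1000, the composite is 20 + 0.021 × 980 = 40.6 against 20 + 0.0103 × 980 = 30.1 per 1000, with power 37% (45% at s = 15, 32% at s = 25).

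**5. Would agreement in direction be enough?** Among simulated trials with a false significant benefit, the composite also favoured the intervention in about 87% to 98%, because it contains the same chance-low neonatal deaths. Agreement in sign would rarely expose the bias.

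**The case against.** Deaths per live birth is the standard definition of neonatal mortality, the protocol uses it consistently, and a supporting analysis could sit in a statistical analysis plan not shown here. The definition is indeed legitimate and should stay. The analysis plan may add such an analysis. The point rests on what this document does fix: the outcome list down to exploratory level, a named additional mortality analysis, and pregnancy loss assigned to safety monitoring.

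The pathway to stillbirth is also uncertain. The protocol hypothesises no such effect, and it reduced the frequency of facility-delivery messages relative to the predecessor programme because facility delivery is already common. Control CHWs are equally unblinded, and nothing describes how eCHIS classifies a death at birth. All of this stands. A reader might infer that differential recording is happening or that the primary result will be biased, but the documents support only the possibility.

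The DSMB sees unblinded safety data and advises on imbalances, so a large difference in recorded pregnancy loss might be noticed. That is a partial safeguard, but not a comparison reported with the primary result.

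Finally, registered pregnancies are not fully protected by randomisation either: facilities were randomised first, and unblinded CHWs register pregnancies afterwards. This limits the alternative and is why it can only support the primary analysis.

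A reader might also take the two descriptions of the 7200 as a sample size error. They are not: the sample size section is explicit and its power reproduces. The abstract is loosely worded.

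**Conclusion.** The concern holds as a design weakness with an inexpensive remedy. The planned mortality analyses cannot separate prevented neonatal deaths from movement between stillbirth and early neonatal death. Under assumed misrecording of 5–20% in one arm, a null ratio moves to 0.95–0.80 and the one-sided error from 2.5% to about 4–16%. Under the assumed averted-stillbirth ranges the bias runs the other way and costs between 1 and 40 percentage points of power. In the ranges tried, neither mechanism alone reaches the planned ratio of 10.3/21.0 = 0.49, so a result of the planned size would not be explained by either. A more modest benefit could be. The documents supply no stillbirth rate and no evidence of differential recording, so these figures show sensitivity and are not estimates of bias.

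**What to change.** - Keep neonatal mortality among live births as the primary outcome.
- Pre-specify one supporting analysis of stillbirth plus neonatal death over all registered pregnancies that reached 28 weeks. Use the same eCHIS extraction and a mixed model with the same facility and CHW random effects, with a pregnancy-level denominator in place of the survival-time offset.
- Report its estimate and confidence interval beside the primary result, together with stillbirths and unknown pregnancy outcomes by arm.
- State in advance that a primary benefit accompanied by excess intervention-arm stillbirths, or by a composite ratio near 1, will be read as possible reclassification. Do not treat mere agreement in direction as reassurance (step 5), and do not require the composite to be significant, given its 32–45% power.
- Make the abstract and the sample size section count the same unit.

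The cost is one more model on records already being abstracted, plus wording. The composite is diluted if stillbirth is unaffected, and its population is also formed after randomisation by unblinded CHWs. It therefore supports the primary analysis and does not replace it.

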#### Methods in the analysis to handle protocol non-adherence and any statistical methods to handle missing data {20c}

Based on the Mobile WACh NEO RCT [41], we expect a 10% loss to follow-up between enrollment and the 6-week study visit. We anticipate that women who are lost to follow-up are more likely to be disengaged from care and have experienced adverse outcomes. We also anticipate missingness may differ by arm, with the intervention arm having higher retention. A secondary analysis of mortality will be performed in which missing mortality at 28 days will be imputed using multiple imputations by chained equations (MICE).

To explore any dose–response effects associated with variation in the fidelity of intervention delivery, we will conduct an exploratory analysis comparing primary and secondary outcomes between participants who received low vs. high fidelity of the intervention, defined based on the number of automated and CHW messages received. Propensity score matching will be used to control for confounding by participant or CHW characteristics.

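### The primary mortality model assumes one constant death rate over 28 days while outcome and power are a 28-day risk; if hazard falls with age and follow-up is longer in the intervention arm, its ratio leans toward the intervention

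*Protocol article*

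**What the plan says.** Under Outcomes {12}, the primary outcome is neonatal mortality, "defined as the death of a live-born infant within 28 days of birth", taken from routine eCHIS records. Table 1 gives its analysis as "GLMM (RE by facility and CHW) with Poisson link and survival time as offset". The binary secondary outcomes in the same table use a Poisson model with robust standard errors and no offset.

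Sample size {14} works on the risk scale. It claims "80% power to detect a difference in neonatal mortality of 21.0 vs. 10.3 per 1000 live births", with 20 clusters averaging 360, and assumes "two-sided tests, 10% attrition, a conservative coefficient of variation of 0.25".

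Section {20c} expects 10% loss between enrolment and the 6-week study visit, with adverse outcomes more likely among those lost. It adds: "We also anticipate missingness may differ by arm, with the intervention arm having higher retention". It then plans multiple imputation of missing 28-day status, as a secondary analysis only. The article does not give the distribution of deaths by day of life, loss by arm, the unit of survival time, or the coding of a death on the day of birth.

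**The concern.** A Poisson model with log survival time as offset and no age term estimates deaths per unit of time and treats every day of the 28 as equally dangerous. If the early days carry most of the risk, infants followed for longer add mainly late, low-risk time. The arm with longer follow-up then shows a lower rate even when true mortality is the same. Since the plan expects better retention in the intervention arm, the error would point toward benefit. The model in question carries the primary result; the imputation that could check it is secondary.

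**Working it through.** **1. The plan's own figure.** Inputs from Sample size {14}: p0 = 0.0210, p1 = 0.0103, 10 clusters per arm, m = 360 × 0.9 = 324, k = 0.25, two-sided α = 0.05. Hayes-Moulton formula for proportions:

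c = 1 + (1.960 + 0.842)² × [p0(1−p0)/m + p1(1−p1)/m + k²(p0² + p1²)] / (p0 − p1)²

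The bracket is 0.0000635 + 0.0000315 + 0.0000342 = 0.0001291, and (p0 − p1)² = 0.0107² = 0.0001145. So c = 1 + 7.849 × 0.0001291/0.0001145 = 9.85, which rounds to 10 per arm. Power at 10 is 80.7%, or 80.1% with a Poisson-rate variance. The stated 80% reproduces on either scale.

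**2. Complete follow-up.** The risk ratio is 0.0103/0.0210 = 0.490. The person-time rate ratio is 0.488 under constant hazard, since ln(1 − 0.0103)/ln(1 − 0.0210) = 0.01035/0.02122. It is 0.485 at the extreme where all deaths fall at time zero. The largest gap is about 1%.

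**3. Unequal follow-up, no true effect.** Assumptions, none of them in the article: a fraction L of an arm is last seen at day 3, and a share f of deaths has occurred by then. Loss is unrelated to death, and the little time removed by deaths is ignored.

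- Deaths observed ∝ (1 − L) + L·f
- Person-time = 28(1 − L) + 3L

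For f = 0.6 and loss of 15% (control) versus 5% (intervention): control 0.94/24.25, intervention 0.98/26.75, ratio 0.945.

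| Share of deaths by day 3 | Loss 12% vs 8% | Loss 15% vs 5% |
|---|---|---|
| 0.50 | 0.982 | 0.956 |
| 0.60 | 0.978 | 0.945 |
| 0.75 | 0.971 | 0.930 |

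Both columns average the plan's 10% loss. Under other assumptions (35% to 50% of deaths on day 0, 75% to 85% in week 1, several patterns of loss time) the ratio was 0.97 to 0.99 and 0.94 to 0.97.

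**4. Constant hazard.** Then f = 3/28, deaths become [28(1 − L) + 3L]/28, exactly proportional to person-time, and the ratio is 1 for any L. Dropping the offset in that case gives 1.02 to 1.04 at 12% versus 8% and 1.05 to 1.11 at 15% versus 5%, so removing it is not the remedy.

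**5. Deaths on the day of birth.** A survival time of exactly 0 gives log(0), and the fit fails. In simulations without random effects, coding such deaths as 0.01, 0.5 or 1 day, or adding a day to all times, gave 0.489 each time, against a risk ratio of 0.493 in the same runs. Dropping them gave 0.492 but raised the standard error of the log ratio from 0.22 to 0.28, assuming 35% of deaths fall on day 0.

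**6. Age bands.** Same example (f = 0.6, 15% versus 5%), with assumed 35% of deaths on day 0 and 75% in week 1. Relative deaths over days at risk:

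- Day 0: 0.35/1 in both arms, ratio 1.000.
- Days 1-6: control (0.25 + 0.85 × 0.15)/(2 + 0.85 × 4) = 0.3775/5.4; intervention 0.3925/5.8; ratio 0.968.
- Days 7-27: control 0.2125/17.85; intervention 0.2375/19.95; ratio 1.000.

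The Poisson estimate θ common to the bands solves Σ[D₁ − θT₁(D₀ + D₁)/(T₀ + θT₁)] = 0, with D and T the deaths and days in each band (subscript 1 intervention, 0 control). It is 0.987, against 0.945 with a single rate. Most of the bias goes; what remains comes from hazard falling within days 1-6.

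**7. Restricting to known 28-day status.** At 21 per 1000 in the same example, control is 0.01974/(0.01974 + 0.85 × 0.979) = 0.02317 and intervention 0.02058/(0.02058 + 0.95 × 0.979) = 0.02165. The ratio is 0.934, further from 1 than 0.945. The same ordering held in all nine combinations of f (0.5, 0.6, 0.75) and loss (12% vs 8%, 15% vs 5%, 30% vs 10%).

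**The case against.** An offset is the standard correction for unequal follow-up, and step 4 shows that it works when hazard is constant and loss is unrelated to death. The bias needs a falling hazard as well as differential loss inside the 28 days, and the article documents neither. The retention forecast concerns the 6-week study visit, counted from enrolment in pregnancy, whereas mortality comes from eCHIS. Loss before delivery with no birth record, or after day 28, does not touch the model, and placing all loss at day 3 is close to the worst case. The planned imputation already offers an analysis on the 28-day scale.

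Most of this stands and limits the size of the point. It does not remove it. Section {20c} goes straight from differential missingness to imputing 28-day mortality, so carrying the forecast over to the primary outcome is a reasonable inference, though still an inference. The same section expects those lost to have had worse outcomes, which is not non-informative loss.

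A reader might also infer that the offset is undefined for deaths on the day of birth. That depends on such deaths carrying a time of exactly zero, which the article does not say. Coding of this kind is commonly left to the full protocol or analysis plan, and any positive value avoids the failure.

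**Conclusion.** The point holds in limited form. A single-rate model is paired with a 28-day risk outcome, and the result is sensitive to follow-up that differs by arm if hazard falls with age. At an average loss near the stated 10%, the expected ratio with no true effect is 0.97 to 0.98 (12% versus 8%) or 0.93 to 0.96 (15% versus 5%), a shift of about 2% to 7% toward the intervention. On the log scale the larger shift is 0.05 to 0.07, against a standard error of about 0.22 before clustering. These figures rest on assumed death timing, loss by arm and day of loss.

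Three stronger readings are not supported. The rate ratio is not biased whenever follow-up differs: constant hazard with non-informative loss gives none, nor does equal follow-up. The net direction is not settled, because unrecorded deaths among lost control infants would push the ratio the other way. And the power claim is not undermined, since it reproduces on either scale.

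**What to change.** Keep the Poisson GLMM and its random effects for facility and CHW. Split each infant's follow-up into age bands, for example day 0, days 1-6 and days 7-27, and add a band effect. Give every death positive time, for example half a day on the day of death. Report the implied 28-day risks per 1000 live births beside the ratio, so that the result is on the scale of the outcome and the power statement. Finer early bands would remove more of the remaining bias.

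Use the already planned multiple imputation of 28-day status as the risk-scale sensitivity analysis. Do not use a yes/no analysis limited to infants with known status for that purpose: it keeps early deaths, discards lost survivors, and in step 7 is more biased than the offset model.

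The cost is slightly more data preparation from the same eCHIS dates and two extra parameters.
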